## Study summary

Study Title: Feasibility and acceptability of a supervised and self-directed technology-based Dual Task training programme for older adults at risk of falling.

Internal ref. no. (or short title): Dual-task training in older adults.

Study Design: A single-arm, non-randomised feasibility study.

Study Participants: adults aged 65 years and above.

Planned Size of recruitment target (if applicable): 50 adults aged 65 years and above.

Follow up duration (if applicable) No follow-up in this study.

Planned Study Period: 24 months.

Research Question/Aim(s): This study aims to examine how feasible it is to deliver a blended supervised and self-directed technology-based dual-task training programme for older adults who have high risks of falling and wish to improve balance and mobility.

We ask:

1. Is a 24-weeks blended supervised and self-directed technology-based DT training programme (using a mobile app) acceptable to older people at risk of falling?

2. Is a 24-weeks blended supervised and self-directed technology-based DT training programme feasible and deliverable, with potential to be adopted by falls prevention services in the NHS?

## Funding and support in kind

| **FUNDER(S)**  (Names and contact details of ALL organisations providing funding and/or support in kind for this study) | **FINANCIAL AND NON FINANCIALSUPPORT GIVEN** |
| --- | --- |
| The NIHR Research for Patient Benefit Scheme | £263,831.00 |

## Role of study sponsor and funder

The sponsor will host the study and hold negligent harm and non-negligent harm insurance policies

## Roles and responsibilities of study management committees/groups and individuals

Patient & Public Involvement Group: [name] is a public co-investigator who will lead the patient and public involvement group and oversee the study to ensure outcomes meet patient benefits and interests. Participants in this study will be invited to a focus group to discuss their perspectives to the study. Discussion will be used for development of a follow-on study.

## Study flow chart

[figure not shown]

# Study protocol

1. Background

The decreasing ability to multitask is associated with increasing risk of falling in older people^1,2^. Falls are a major public health burden, with the prevalence increasing with age. Around 1 in 3 adults aged over 65, and half of people aged over 80 have at least one fall a year, and in half of such cases the falls are recurrent^3^. The most common mechanisms of major trauma or poly trauma presenting to A&E in the UK are falls^4^. Falls can lead to severe consequences such as hip fracture and loss of independence; 1/3 of individuals with a hip fracture die within a year^5^. An estimated £4.4 billion per year is spent on treating fractures and fall-related injuries^3^. Given the ageing population in the UK and the projected increase in the number of people aged 85 years and above from 1.6 million in 2016 to 3.2 million by 2036, falls prevention in older people is vital^6^.

1. Rationale

We often multitask in daily living; for example, walking while texting or reading the news while making our morning coffee. The ability to multitask, i.e., for our brain and body to work at the same time, declines with ageing. Reduced ability to multitask increases the risk of falling in older people. Research shows that training both the brain and body at the same time improves multitasking performance and mobility, thereby reducing the risk of falling^7-9^. There is evidence that some mind-body training programmes, delivered via mobile applications on tablets and smartphones, can improve mobility and the ability to multitask, and are therefore value for money^10-13^. Suitable cognitive (mind) and physical exercises can be pre-selected into a mind-body training programme, allowing people to self-direct their exercise independently while at home.

According to the conversations we had with older people who have had a fall previously and are worried about falling again, a technological, home-based exercise programme can appear daunting to older people. They have acknowledged that they may have lower levels of experience, skills, knowledge or competence in using technology, and as a result they may be reluctant to engage with such initiatives. This study proposes a blended method combining both a supervised and a self-directed mind-body training programme, with the use of technology via a mobile app. This project will examine how acceptable this new programme is likely to be to older people at risk of falling and will evaluate the feasibility of delivering it within the NHS.

1. Theoretical framework

A systematic review and meta-analysis^8^ including 30 RCTs concluded that supervised DT training in hospital or community settings (without technology) is superior to single-task (balance or resistance) training or no training for improving Timed Up and Go speed (standard mean difference [SMD] = −0.22 [95% CI:−0.38 −0.06], P = 0.007) and reducing fall rates (SMD (95% CI) = −3.03 (-4.33, -1.73), P = 0.007). Training the cognition and physical function simultaneously rather than sequentially is more beneficial^14,15^. Simultaneous cognitive and physical training can easily be delivered via technology (e.g., mobile apps), enabling professionals to select cognitive exercises that are suitable to be combined with balance exercises, allowing for the DT training to be delivered unsupervised at home. Mobile apps are interactive, provide instant feedback, and can send reminders to users. These features promote engagement and adherence to exercise^16^.

Our observational study showed improved balance after a home-based DT training programme with a mobile app in older adults without a history of falls and the adherence rate over the 6-weeks training period was 90%^12^. A recent, underpowered RCT with older people in Australia reported a trend for improvement in walking speed after a homebased DT programme via tablets^11^. These findings support the notion that technology-based exercise (not limited to DT exercise) may be a sustainable means of promoting physical activity and preventing falls in older people^17-19^. However, the evidence is not definitive in how sustained the engagement and the effectiveness of the DT training programme with technology can be. This study contributes to the need to identify a delivery method for home-based exercise using mobile apps that is acceptable to older people and has the potential to be adopted by the NHS.

1. Research question/aims
   1. Research aim

- This study aims to examine how feasible it is to deliver a blended supervised and self-directed technology-based DT training programme for older adults who have high risks of falling and wish to improve balance and mobility.
  1. Research questions
- Is a 24-weeks blended supervised and self-directed technology-based DT training programme (using a mobile app) acceptable to older people at risk of falling? Secondary research questions
- Is a 24-weeks blended supervised and self-directed technology-based DT training programme feasible and deliverable, with potential to be adopted by falls prevention services in the NHS?
  1. Outcomes

The primary outcome will be the feasibility of a subsequent phase III trial according to pre-specified progression criteria. We are primarily interested in whether the study is appealing to participants (assessed by the recruitment rate) and if the intervention is acceptable (measured by adherence and usage of the app).

The decision of whether to continue to the phase III trial will be decided by pre-defined stop-go criteria, based on the following definitions and criteria:

- Recruitment via NHS fall prevention service and in community: Defined as the number recruited/number approached (x100%). Via the planned focus groups, we will investigate whether the recruitment route chosen in this study is appropriate for the main trial.
- Adherence: Defined as the number of actual exercise days/number of exercise days offered (x100%) (60 days in total offered: 2 days/week x 12 weeks in phase 1 + 3 days/week x 12 weeks in phase 2) based on the exercise calendar.
- Usage of the app: Defined as the number of days used/number of days offered (x100%) and a self-reported online EXIT survey designed based on the feasibility assessment framework.
- Attrition: Defined as withdrawal from the study and/or no follow-up data available.

The secondary outcome measures will be: 1) Timed up and Go with and without a cognitive task, 2) everyday Cognition scales short version, 3) Falls Efficacy Scale-International, 4) Health questionnaire EQ-5D-5L, 5) Use of healthcare service via ModRUN, and 6) Self-reported numbers of falls.

1. Study design and methods of data collection and data analysis
   1. Study design

A single-arm, non-randomised feasibility study.

- 1. Recruitment

Recruitment will be carried out through the NHS falls prevention services, GP practices, and in community.

*NHS recruitment*

We will recruit from outpatient falls clinics at University Hospitals Birmingham and falls prevention services at the Birmingham Community Healthcare NHS Foundation Trust and Birmingham and Solihull Clinical Commissioning Group. These services receive patients living in different areas of Birmingham and Solihull, allowing recruitment of a diverse population. Additionally, e-searches on database of the NHS primary care in the West Midlands will be carried out by the primary care team of the CRN West Midlands. Text messages will be sent out to eligible participants.

For the site of Birmingham Community Healthcare NHS Foundation Trust and the GP practices in the West Midlands, a mail-out approach or SMS text messages will be used and carried out by an appropriate team in the Trust. Eligible participants will be identified from the database and sent a study flyer with the contact information of the research team for which they can reach out and enquire the study. Consent to enter the study will be sought at a community centre where the baseline assessment is being conducted.

For the other sites, adults meeting the eligibility criteria will be approached by a clinician in the falls clinic and provided with a study information leaflet which contains study information and contact details of the research team. The clinician may inform the research team that the participant has agreed to take part in the study and has agreed to be approached. The research team will then approach the participant to answer questions they might have and complete informed consent procedures. Alternatively, the participant can ring the research team to express willingness to take part and/or ask questions.

Furthermore, we will recruit 30 healthcare professionals working in the NHS falls prevention services in England and Wales for focus groups. We will advertise the study participation opportunity via professional bodies and social media.

Community recruitment

We will put up the study flyer in retirement homes, book clubs, etc in the West Midlands. Potential participants will be able to self-refer to members of the research team.

- 1. Planned interventions

A summary of the blended DT intervention is in Table 1:

Table 1. Summary of the blended DT exercise training programme.

|  | Supervised group exercise | Self-directed, home-based exercise |
| --- | --- | --- |
| Phase 1 – week 1-12 | **Duration:** 45 minutes  **Location:** local leisure/wellbeing centres  **Frequency:** one class/week  **Content:** 10 minutes warm-up, 30 minutes of DT training, 5 minutes cool down, followed by refreshment.  **DT training:**   - Cognitive exercises delivered via the PEAK app. - Strength and balance exercises delivered by a physiotherapist | **Duration:** 45 minutes  **Location:** at home  **Frequency:** twice/week  **Content:** 10 minutes warm-up, 30 minutes of DT training, 5 minutes cool down.  **DT training:**   - Cognitive exercises delivered via the PEAK app. - Strength and balance exercises in an exercise booklet |
| Phase 2 – week 13-24 | No supervised group exercise | **Duration:** 45 minutes  **Location:** at home  **Frequency:** three/week  **Content:** 10 minutes warm-up, 30 minutes of DT training, 5 minutes cool down.  **DT training:**   - Cognitive exercises delivered via the PEAK app. - Strength and balance exercises in an exercise booklet |

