**Phase 2 – self-directed, home-based DT training programme 3 days/week for 12 weeks.**

Participants will undertake 30 minutes of self-directed DT exercises at home 3 times per week for 12 weeks. They will perform the DT exercise using the PEAK app and the strength and balance exercises in the exercise booklet. Usage and engagement of the app of the participants will continue to be recorded by the app. Participants will record their exercise adherence in the exercise calendar. Participants can contact the research team for technical assistance.

All participants will be contacted in week 24 to attend a post-assessment session in week 25. Their travel expenses for attending the post-assessment will be met.

End of Phase 2 (Week 25) – post assessment and app data extraction session.

Participants will be invited back to the same place of the exercise classes to undergo the TUG assessment. The research team will perform the TUG assessment and document the app usage data from week 13 to week 24 from participants’ phones/devices. The exercise calendars will also be collected from the participants. All participants will be sent the same online questionnaires as they completed at baseline and at the end of the phase 1 and asked to complete the questionnaires within 2 weeks from the post-assessment.

- **Qualitative interviews and focus groups**

Five face-to-face focus groups (FGs) with a total of 30 participants who have completed the programme (4-6 participants per group for 45-60 minutes) will be conducted. We will purposefully sample 30 participants, based on the demographic information, geographic location, exercise adherence, and results of the EXIT survey, to attend the focus groups.

Additionally, we will conduct five online FGs with a total of 30 healthcare professionals, including GPs, district nurses, paramedics, and physiotherapists who are part of the NHS falls prevention care pathways in Birmingham and Solihull, via MS Teams. Clinicians and physiotherapists involved in this study will be invited to take part.

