The purpose of conducting the FGs is to allow for in-depth exploration of the results obtained from the feasibility study as well as to capture attributes of the acceptability and feasibility which are unable to be recorded by outcome measures stated in the feasibility study above. Questions will be developed based on the framework for qualitative research in feasibility studies for trials^23^ and input from the PPI group. Specifically, questions will cover 4 main categories:

- - Intervention content and delivery
  - Study design, conduct and processes
  - Outcomes (e.g., are they important to service users?)
  - Measures (e.g., are the process valid for the service users?)

Descriptive data from the adherence, usage of the app, and the EXIT survey will be used as prompts. The FG will be led by two members from the study team. The reason to have two people leading the FGs is to ensure both verbal and non-verbal interactions and group dynamics during the discussions can be documented^40^.

FGs will be voice recorded and later transcribed and analysed using a deductive thematic approach with Nvivo9 software; data for the study participants and the stakeholders will be analysed separately.

- 1. Assessments

**Primary outcomes:** Whether the study is appealing to participants (assessed by the recruitment rate) and if the intervention is acceptable (measured by adherence and usage of the app).

1. Recruitment via NHS falls prevention services and in community. The recruitment rate [(number recruited/number approached) x100%] will be assessed. Via the planned focus groups, we will investigate whether the recruitment route chosen in this study is appropriate for the main trial.

1. Usage of the app during the 24-weeks blended DT training programme:
   1. Numbers of days undertaking both cognitive and physical exercises and numbers of exercises completed, assessed via data extracted from the PEAK app cloud and recorded on the exercise calendars. App-recorded and self-reported adherence to the DT exercise will be compared to inform how to best record exercise adherence in the full trial.
   2. Types of cognitive exercises completed with the physical exercises, evaluated via the data extracted from the PEAK app, to provide information on content design of the DT training programme in the future.
2. Study retention rate: [(number completed study/ number recruited) x100%] will be assessed.

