The analysis undertaken within this feasibility study will mainly be descriptive. The progression criteria in the stop-go will be summarised as proportions and percentages with 95% confidence intervals. The numbers of days of exercise and the numbers of exercises completed recorded in the app and on the exercise calendars during the 6-month intervention period will be summarised to describe the usage of the app and adherence. To understand any change in the usage of the app between phase 1 and phase 2, we will assess the app usage in phase 1 and phase 2 separately. Information from the EXIT survey will be summarised.

Outcome measure data will be summarised at baseline and follow-up using appropriate summary statistics. Exploratory analysis may compare the data from the two time points using a paired t-test (depending on the distribution of the data) to provide preliminary data on the effects of the blended intervention.

1. Study setting

Participant identification will be carried out in falls clinics at University Hospitals Birmingham (Queen Elizabeth Hospital Birmingham, Birmingham Heartlands Hospital, and Solihull Hospital) and falls prevention services at the Birmingham Community Healthcare NHS Foundation Trust and Birmingham and Solihull Clinical Commissioning Group.

Participant recruitment will be conducted in two ways: 1) a mail-out approach for the Birmingham Community Healthcare NHS Foundation Trust, and 2) by clinicians from the University Hospitals Birmingham and Birmingham and Solihull Clinical Commissioning Group.

Study consent will be performed either at the clinics or in the community by the study team. Members of the team who will be carrying out study consent and data collection will undergo GCP training.

Interventions and assessments will be conducted in the community by the research team.

1. Participant recruitment

Adults aged 65 years and above who have fallen more than once in the past 12 months and are referred to undertake exercise for managing their fall risks.

- 1. Eligibility Criteria
     1. Inclusion criteria

Patients will be recruited if they:

1. Aged 65 years and above,
2. Can give informed consent,
3. Demonstrate sufficient cognition/hearing/vision to follow instructions of the assessment and the exercise programme,
4. Can stand with one hand support on the current walking aid for at least 60s,
5. Can stand up from a chair independently and walk for 6 meters independently with the current walking aid,

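### Suitability of the recruitment route is left to focus groups of programme completers, beside one pooled recruitment rate, so a weak route could be masked

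*Protocol*

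**What the plan says.** **The question and the means.** Section 4.3 places recruitment among the stop-go criteria and adds: "Via the planned focus groups, we will investigate whether the recruitment route chosen in this study is appropriate for the main trial". Section 5.4 repeats this after stating: "The recruitment rate [(number recruited/number approached) x100%] will be assessed". In both places there is one ratio, covering the NHS and the community together.

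**The routes.** Section 5.2 opens: "Recruitment will be carried out through the NHS falls prevention services, GP practices, and in community". It then describes personal approach by falls-clinic clinicians, mail-out or SMS for the community Trust and GP practices, and self-referral in the community: "We will put up the study flyer in retirement homes, book clubs, etc in the West Midlands". Section 6 says "Participant recruitment will be conducted in two ways" and lists only the Trust mail-out and the clinicians. Section 7.3.1 names only falls clinics and falls prevention services.

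**The focus groups.** Section 5.3 plans: "Five face-to-face focus groups (FGs) with a total of 30 participants who have completed the programme". Selection is described as: "We will purposefully sample 30 participants, based on the demographic information, geographic location, exercise adherence, and results of the EXIT survey". Route of entry is not among these factors. Five online groups with 30 healthcare professionals are also planned, and clinicians involved in the study are invited.

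**The analysis.** Section 5.5 summarises the progression criteria as overall proportions with 95% CIs. The only breakdown it names is app usage by phase.

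**The concern.** Whether a route suits the main trial depends mostly on how many of the people it reaches are recruited and stay. The people who know why a route failed are those who ignored the text, declined in clinic or never rang. None of them can be in a patient focus group, because those groups are restricted to completers. Nor does the sampling ensure that each route is represented among the completers who are chosen.

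The quantitative result beside the focus groups does not fill the gap. A single pooled ratio averages routes that reach people very differently: a clinician's personal request, a text from a database search, and a poster. If one route does well and another poorly, the average can look acceptable, and a multi-route strategy could be carried into phase III with a component that contributes little.

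The route lists add to the difficulty. The protocol speaks of the route in the singular, and sections 5.2, 6 and 7.3.1 do not agree on which routes are used. It is therefore unclear what the focus groups are to judge.

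**Working it through.** **1. The plan's own precision figures (7.2.1).** Half-width = 1.96 × √(p(1 − p)/n).
- Participation, p = 0.50, n = 100: 1.96 × √(0.25/100) = 0.098, matching the stated ±9.8%.
- Attrition, p = 0.20, n = 50: 1.96 × √(0.16/50) = 0.111, matching the stated ±11%.

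Both are correct, and both apply to rates pooled over all routes.

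**2. Who can be in a patient focus group.** Take the plan's own values, and assume that those not lost to attrition count as completers.
- 100 identified × 50% = 50 recruited.
- 50 × (1 − 0.20) = 40 completers, of whom 30 are sampled.
- So 50 people not recruited and 10 lost, 60 of the 100, are outside the groups by design.
- 40 − 30 = 10 completers are left out. If four routes contributed equally, each would supply 50/4 = 12.5 entrants and 12.5 × 0.8 = 10 completers. Because route is not a sampling factor, nothing in the plan would prevent one such route from being absent.

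**3. Can a pooled rate hide a weak route?** The protocol gives no split by route, so these counts are assumed. Intervals are Wilson 95%: (p + z²/2n ± z√(p(1 − p)/n + z²/4n²)) / (1 + z²/n), with z = 1.96.

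| Route A | Route B | Pooled |
| --- | --- | --- |
| 40/50 = 80% (67% to 89%) | 10/50 = 20% (11% to 33%) | 50/100 = 50% (40% to 60%) |
| 48/80 = 60% (49% to 70%) | 2/20 = 10% (3% to 30%) | 50/100 = 50% (40% to 60%) |

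Worked for 10/50: (0.20 + 0.0384 ± 1.96 × √(0.0032 + 0.000384)) / 1.0768 = (0.2384 ± 0.1173) / 1.0768, giving 0.112 to 0.330.

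In both rows the pooled figure is exactly the 50% labelled green. The per-route figures, rough as they are, show the weak route.

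**4. Precision per route.** If the 100 were divided evenly (assumption), the half-width at p = 0.50 would be:
- two routes, n = 50: ±13.9 points
- three routes, n = 33.3: ±17.0 points
- four routes, n = 25: ±19.6 points

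That is enough to describe a large shortfall, but not to rank routes that are close.

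**5. Denominators.** People approached in clinic, mailed or texted can be counted. For flyers in retirement homes and book clubs the protocol describes no count of people approached, so recruited over approached cannot be formed for that route as written. The first countable step there is the enquiry.

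**The case against.** The case for leaving the text alone has four parts.

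**The protocol says investigate, not decide.** The sentence follows a quantitative rate, and section 5.3 gives the groups the task of exploring the study's results in depth. A reader might infer that the phase III route will be chosen on focus-group opinion alone. The documents do not say that, and the point does not rest on it.

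**Professionals are included.** Clinicians who approach patients in person may see refusals and can report them. A reader might therefore go too far in concluding that a poor route cannot be detected at all. Some problems could surface this way. The help is partial: the community flyer route has no clinician observer, and nothing in the protocol supplies the professionals with uptake by route.

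**The SAP may tabulate by route.** It may, and a missing table would not by itself be a finding. But a table needs route and numbers approached to have been recorded when contact was made. The protocol provides for neither, and both may be hard to reconstruct later.

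**Numbers are small.** This stands. A reader might also infer that the routes differ in retention. The protocol gives no data on that, and the study could hardly show it. With an assumed 2/20 lost (10%, exact 95% CI 1% to 32%) and 8/30 lost (27%, 12% to 46%), the pooled figure is 10/50 = 20%, the attrition value labelled green. The intervals overlap widely and Fisher's exact p is 0.28. Per-route figures can describe, not test.

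**Conclusion.** The point holds as a worthwhile, low-cost improvement. The protocol gives the question of route suitability to focus groups whose patient members all completed the programme and are not sampled by route. It defines only a pooled recruited-over-approached rate although several routes are in use. A route recruiting 10% or 20% could therefore be masked within a pooled 50%. That illustration rests on assumed splits; the protocol gives none, and nothing in it shows that any route will in fact perform poorly. The stated precision figures are correct.

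The differing route lists in sections 5.2, 6 and 7.3.1 are an inconsistency in the current text and need reconciling in any case. They do not themselves show that the focus-group method fails.

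**What to change.** In 4.3 and 5.4, keep the pooled rate and replace the focus-group sentence with wording such as:

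*Route of entry (clinician approach, Trust mail-out or SMS, GP text message, community flyer with self-referral) is recorded at first contact. Numbers approached, mailed or texted (where countable; no denominator exists for flyers), enquiring, eligible, consented and retained at week 25 are reported by route, descriptively and with 95% confidence intervals, alongside the pooled rate. These counts are read together with focus-group views when judging the route for the main trial.*

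In 5.3, add route of entry to the focus-group sampling factors. Reconcile 5.2, 6 and 7.3.1 so that all three give the same routes.

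The cost is one data field, a tally of invitations sent by each route, one extra table and the wording change. The field should be in place before first contact, or as early as possible. The downside is imprecision: per-route figures will be descriptive, should carry their intervals, and cannot support a formal comparison of routes.
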